### 8.2.2 Prophylactic mastectomy samples

For women planning to undergo prophylactic mastectomy, no second VAB biopsy is required. However, these women will require take UA up to and including the day of their operation. At mastectomy an orientation clip will be placed as per normal practice. Following the mastectomy procedure the excised breast will be transported fresh to the breast pathologist at MFT and the area best correlating to the most dense area on mammography (broadly identified by breast quadrant) will be excised and divided into liquid nitrogen, formalin and culture medium as described in 4.5.1 above. At least 1gm of tissue will be harvested for analysis although there is no restriction on the amount of tissue that can be returned to the Breast Biology Group laboratory in these cases.

## 8.3 Radiological Assessments

Baseline mammography will be analysed using Volpara™ and the breast density will be correlated with the subsequent MRI-derived measurements. Serial MRI will be used to correlate biological with radiological changes. The fibroglandular distribution for each breast at baseline MRI will enable identification of areas of comparable density for biopsy at each time point. The MRI examinations will be performed in the 7 days prior to the expected onset of menses on a 1.5T Philips MRI scanner using a dedicated multichannel breast coil. A dynamic contrast-enhanced protocol will be used with the recommended body weight-adjusted dose (0.1mmol/kg) of intravenous gadolinium-containing contrast medium delivered via a pump injector. The images will be viewed on a modality workstation and/or PACS workstation. Further image analysis will be performed on a

workstations running image analysis software. Image segmentation will be performed to determine fibroglandular and overall breast volumes. Background parenchymal enhancement will be measured both visually and using standardised regions of interest (ROIs). In addition,  $K_{trans}$ ,  $v_e$  (extracellular/leakage space),  $v_p$  (vascular volume), fibroglandular apparent diffusion coefficient and fractional anisotropy, water/fat ratio and T1 and T2 relaxation times will be measured.

Ultrasound elastography will also be performed immediately prior to the vacuum biopsies. This will be with a Siemens S3000 ultrasound machine utilising acoustic radiation force imaging (ARFI) with a 9Mz probe. Measurements of fibroglandular and fat tissue stiffness will be performed in each of the four quadrants of both breasts, targeting the densest and least dense area in each quadrant respectively. Changes in tissue stiffness between pre- and post-treatment scans will be explored and correlated with the MRI data.

Another potentially useful measure of responsiveness of the breast to preventive therapy is change in the electrical conductance of the breast. It depends on differences in electrical impedance between fat and glandular/stromal tissue. It has not been widely investigated but has the potential value of simplicity and repeatability and, depending on further studies, has the potential to detect change early.

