### **2.2. Progesterone and the human breast**

In the normal human breast the two PgR isoforms (PRA and PRB) are co-expressed at comparable levels. Relative loss of PRB is seen with the development of atypia or malignancy and in women with germline mutations in BRCA1 or 2 (Mote 2002). Women with such mutations have double the serum progesterone levels compared to age matched wild-type controls (Widschwendter 2013). The combination of estrogen and progestin as hormone replacement therapy (E+P HRT) significantly increases BC incidence and mortality whereas estrogen alone (E-HRT) does not (Anderson 2004; Chlebowski 2003; Chlebowski 2010; Beral 2003). In premenopausal women breast epithelial cell proliferation is highest in the progesterone dominant luteal phase of the menstrual cycle and can be reduced by the antiprogestin mifepristone, although this drug has now been discontinued due its hepatic toxicity (Engman 2008; Potten C 1988; Pike 1993; Navarrete 2005).

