**MRI visit (day – 7 ± 4 days EOM to OM)**

During this visit:

- The participant will be asked if they are happy to continue in the trial
- The participant will undergo an MRI scan

If a participant is unable to tolerate the MRI scan, for example due to claustrophobia, she may continue on study and undergo all other trial procedures. In addition, should a participant not fulfil the size/weight requirements of the scanner or if the scanner breaks down resulting in a participant not having an MRI scan they can continue with other trial procedures.

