**VAB visit (day – 7 ± 4 days EOM to OM)**

During this visit:

- Eligibility must have been confirmed by the PI or delegated individual prior to the VAB and provision of the IMP to the participant.
- The participant will be asked if they are happy to continue in the trial
- Any changes to the participant's concomitant medications will be documented
- Adverse events from the MRI visit or any other adverse events will be documented
- 3x 28 day pack supply of 5mg UA will be supplied to the participant who will be instructed to wait for a telephone call from the study team before starting the medication. Participant will also be given a study card with the medication supply
- The patient will undergo breast electrical impedance measurement
- The patient will undergo the VAB of one breast
- H&E pathological analysis of breast tissue to exclude invasive cancer and Ductal carcinoma in situ (DCIS), If the results of the H&E pathological analysis are not clear, one of the Study Doctors will contact the participant to discuss this with them.

If invasive cancer or DCIS are identified the participant will be discussed at the MFT NHS breast Multi-disciplinary Meeting within 1 week and managed according to standard NHS practice thereafter. Such participants will not be eligible to continue on study.

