**Telephone call to patient regarding histology results and onset of menses**

- The participant will be asked if they are happy to continue in the trial and the importance of using contraception throughout the trial will be emphasised.
- Adverse events from the VAB visit or any other adverse events will be documented
- The participant will be asked if they have started their period

- If the participant has started their period, and there is no evidence of cancer or DCIS on the breast biopsy, they will be instructed when to start study medication . This will be within 1 week of onset of menstruation (OM), in line with the UA SPC.
- If the participant has not started their period then they will be instructed to contact the research team at the OM or on the next working day (M-F) and they will be advised when to commence study medication (UA). If the participant has not phoned by a maximum of 5 days past her EOM then the research team will contact her to ask if she has started her period. If so then she will be asked the date of OM and will be advised when to start UA. If the participant has still not started their period she will be asked to contact the research team again as above. In line with the UA SPC treatment should be started within 1 week of OM.
- The day the study medication is started will be counted as day 1 for visit schedule purposes
- The first visit on treatment (visit 1) will be scheduled during this phone call to fall on day 29 +4/-7 days
- If the results of the H&E pathological analysis were not clear, one of the Study Doctors will contact the patient to discuss this with them

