### **MRI 2 visit Day 78-85**

During this visit the participant will :

- be asked if they are happy to continue in the trial
- undergo an MRI scan

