**VAB 2 visit/ Prophylactic Mastectomy visit Day 78-85**

During this visit the participant will:

- be asked if they are happy to continue in the trial
- have any changes to their concomitant medications documented
- the patient will undergo breast electrical impedance measurement
- have any adverse events documented including those from MRI 2 and be asked whether they have had any vaginal bleeding.
- undergo the VAB of the breast that was not biopsied at baseline or Prophylactic Mastectomy

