## **8 Methodology**

### **8.1 Timing of study entry by luteal phase progesterone**

Luteal progesterone levels will be checked 7 days prior to the expected onset of the next menstrual cycle. The serum progesterone level must be  $\geq 15\text{nmol}$  to confirm an ovulatory menstrual cycle for further trial related procedures to take place. If the level is  $< 15\text{nmol}$  then one further measurement may be taken in the following menstrual cycle (again at day 7 prior to expected onset of menses). If the progesterone level on the second occasion is  $< 15\text{nmol}$  then screening has failed and the woman will not be permitted to enter the study.

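### MRI 2 has two timing rules that cannot always both be met, and on-treatment tissue is timed by drug day while baseline tissue is luteal, which biases Ki67 and BPE modestly towards a fall

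*Protocol*

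**What the plan says.** **Baseline.** Section 7.1 places both the first MRI and the first biopsy between day -7 ± 4 relative to expected menses and its actual onset. Ovulation must be confirmed first. Under Section 8.1, "Luteal progesterone levels will be checked 7 days prior to the expected onset of the next menstrual cycle", and the value must be at least 15 nmol. Baseline tissue and images are therefore luteal by design.

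**On treatment.** Section 7.1 heads the later visits "MRI 2 visit Day 78-85" and "VAB 2 visit/ Prophylactic Mastectomy visit Day 78-85". In the telephone-call visit, "The day the study medication is started will be counted as day 1 for visit schedule purposes", and dosing may begin up to one week after the onset of menstruation. Neither on-treatment visit carries a cycle condition.

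**The MRI rule in Section 8.3.** In a paragraph on serial MRI, "The MRI examinations will be performed in the 7 days prior to the expected onset of menses". The wording is plural and is not limited to baseline.

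**Why phase matters.** Section 2.2 states: "In premenopausal women breast epithelial cell proliferation is highest in the progesterone dominant luteal phase of the menstrual cycle". Section 2.3 says background parenchymal enhancement (BPE) is higher in the luteal than in the follicular phase. Section 5.4.1 expects UA 5 mg to stop ovulation in 70-80% of women.

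**Analysis.** Section 10 applies a Wilcoxon signed rank test to the Ki67 change in all 30 women. Amenorrhoea and on-treatment progesterone enter only as exploratory Mann-Whitney comparisons between subgroups.

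**The concern.** Two problems arise from the same timing rules.

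The first is textual and concerns MRI only. One section times the scans by the menstrual cycle and another times MRI 2 by drug day. A site cannot always satisfy both. Once UA has stopped a woman's periods, an expected onset of menses is not defined.

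The second concerns inference and touches both Ki67 and BPE. Every baseline sample comes from the phase in which the protocol says proliferation and BPE are higher. A woman who keeps cycling on UA may be sampled in any phase at Day 78-85. A change of phase from a luteal baseline can only go one way, towards lower values. There is no control arm against which to subtract it, and the primary test pools everyone.

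**Working it through.** **1. Do the two MRI rules agree?** Cycle day = ((start lag + drug day - 1) mod cycle length) + 1, where the lag is days from onset of menses to first dose (0-7, Section 7.1) and the drug day is 78-85.

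| Cycle length (assumed) | Lag | Cycle days at drug days 78-85 | Last 7 days of the cycle? |
|---|---|---|---|
| 28 | 0 | 22-28, then 1 | Yes, for days 78-84 |
| 28 | 7 | 1-8 | No |
| 25 | 0 | 3-10 | No |
| 25 | 7 | 10-17 | No |

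In a 25-day cycle none of the 64 combinations of lag and day (8 × 8) meets the Section 8.3 rule. The rules are compatible for some women and incompatible for others.

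**2. How many women may still ovulate?** 30 × (1 - 0.80) = 6, and 30 × (1 - 0.70) = 9.

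**3. How often is a still-cycling woman out of phase?** I took lags 0-7, cycles of 25-31 days and drug days 78-85, all equally weighted (assumptions): 8 × 7 × 8 = 448 combinations. In 234 (52.2%) the visit falls in the last 14 days of the cycle and in 143 (31.9%) in the last 7. So 47.8% fall outside the last 14 days. Expected number out of phase: 6 × 0.478 = 2.9 to 9 × 0.478 = 4.3, or about 3-4 women. The share depends strongly on cycle length: 28 of 64 combinations are luteal for a 28-day cycle, 4 of 64 for 26 days and 61 of 64 for 30 days.

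**4. What does this do to the primary test?** The protocol does not give the size of the luteal-follicular difference in Ki67, so a ratio of 1.5 to 3 is assumed. The simulation used N = 30, no drug effect, log-normal Ki67 with between-woman CV 0.5 or 0.7 and within-woman CV 0.5, and a two-sided 5% Wilcoxon signed rank test, counting significant falls (nominal 2.5%). There were 4,000 trials per cell.

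| Women shifted | Ratio 1.5 | Ratio 2 | Ratio 3 |
|---|---|---|---|
| 3 | 3.8-4.7% | 5.0-5.8% | 6.9-7.1% |
| 4 | 5.5-5.6% | 6.9-7.2% | 8.4-8.5% |

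A separate run, with SD of the within-woman log change from 0.3 to 0.8, gave 4-9% for 3 women and 5-21% for 5.

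**5. How large a false fall?** If shifted women have average baselines, the expected fall in mean Ki67 is (number shifted / 30) × (1 - 1/ratio). This runs from 3/30 × (1 - 1/1.5) = 3.3% to 4/30 × (1 - 1/3) = 8.9%. The mifepristone study cited in Section 10 fell from 5.76 to 0.79, which is 4.97/5.76 = 86%.

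**The case against.** **The premenstrual rule does not cover tissue.** This stands. A reader might infer that the Day 78-85 biopsy also breaches Section 8.3. It does not, because that rule names MRI examinations only and no premenstrual rule is set for the second biopsy or mastectomy.

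**The inflation is small.** This also stands. A reader might assume that all 30 women keep cycling under an inert drug, and so reach false-positive rates of 24-72% for the same phase ratios. The documents do not support that case, since Section 5.4.1 expects most women to stop ovulating. In those women, losing the luteal phase is part of the drug's action, not bias.

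**The 48% rests on soft inputs.** This stands in part. Women not yet bleeding are told to ring at onset or on the next working day, so short lags may be commoner than equal weights imply. Section 5.6.3 expects delayed menses and irregular bleeding, so cycle lengths may not persist on UA. Short lags help at 28 days but not in shorter cycles.

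**Phase is already examined.** Visit 3 repeats progesterone and asks about bleeding, and Section 10 names comparisons by amenorrhoea and progesterone. Those compare subgroups with each other. They do not show whether the overall fall persists without phase-mismatched women.

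**A sensitivity analysis belongs in the SAP.** That is a fair point, and its absence from Section 10 alone would be no finding. Visit timing and what the CRF captures are protocol matters, however, and the analysis needs a dated bleed that the protocol does not ask for.

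**Conclusion.** The concern holds in limited form. For MRI 2, Sections 8.3 and 7.1 conflict for late starts and short cycles, and the Section 8.3 rule is undefined in amenorrhoeic women. For Ki67 there is no conflict of text. The design pairs a luteal baseline with an on-treatment sample timed only by drug day.

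The resulting bias is modest and favours UA: about 3-4 of 30 women out of phase, and roughly a 4-9% chance of a significant fall under no drug effect against 2.5% nominal. These figures rest on the protocol's 70-80% anovulation and on assumed cycle lengths, equal weights, phase ratio and variability. A reader might go further and infer that a positive result could be wholly a phase artefact. The arithmetic does not support that for a fall anywhere near the one in the mifepristone study. It matters more for a small fall, and for BPE, where the protocol gives no size for the phase effect.

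**What to change.** 1. Reconcile Sections 8.3 and 7.1 so that one timing rule governs MRI 2, and state what it means for a woman without periods. The same edit should cover the baseline scan, whose Section 7.1 window opens up to 11 days before expected menses (7 + 4) against 7 in Section 8.3.
2. At visit 3, record on the CRF the start date of the last menstrual bleed, kept apart from spotting.
3. Add to Section 10 a supportive sensitivity analysis. It should repeat the primary Ki67 test and the BPE test without women whose bleeding record shows continued regular menses and who were not luteal at Day 78-85. Women who are anovulatory or only spotting stay in. Low progesterone and irregular bleeding are expected UA effects, so excluding on a recent bleed plus low progesterone alone could remove genuine responders.
4. Report it beside the primary result, and state that a fall confined to phase-mismatched women cannot be ascribed to UA. It should not be a pass/fail gate.

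The cost is one CRF date, one extra analysis, about 3-4 fewer women in that analysis, and some misclassification of phase. Visit 3 progesterone is already drawn.

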#### 4. Trial Summary

A summary of trial procedures is provided in Appendix 4.

30 premenopausal women at moderate to high risk of BC (NICE guidelines) will be recruited from family history clinics in a similar manner to previous successful biopsy and dietary intervention studies (Ong 2009; Evans 2010), using mailshot and clinic visit recruitment. Subjects will be confirmed to be in an ovulatory menstrual cycle prior to performance of baseline breast MRI scan and vacuum assisted biopsy (VAB) of the most dense region of one breast. Ideally 10 cores of breast tissue will be taken. After the onset of the next menstrual cycle subjects will start UA 5mg daily and be reviewed every 4 weeks in trial clinics for blood tests and toxicity assessment. In the 12th week of therapy subjects will have a repeat breast MRI scan followed by either VAB of the contralateral breast or prophylactic mastectomy with harvest of breast tissue (from the predetermined contralateral isodense region from baseline MRI). UA will then be discontinued and one further safety visit planned for 4 weeks post completion (figure 2).

Once the participant has had their visit 4 appointment they will be sent an invite to provide a saliva sample for the purpose of DNA analysis. Should they wish to participate in this part of the study a telephone appointment will be made for them. At this appointment a study doctor will discuss the analysis which will be undertaken. Following the discussion, if the participant is happy to proceed, they will be sent a consent form to complete and return to research team.

Once the consent form has been received by the study team, a helix tube for saliva collection will be posted to the participant. The participant will be provided with a return envelope to post the sample to the genetics team at St Mary's Hospital, Manchester.

When the results of the DNA analysis are available an appointment will be made for the participant to be reviewed either as a telephone appointment or to attend the Nightingale Centre for feedback with a study doctor.

Figure 2: Trial schema

[figure not shown]

The end of the trial will be when the last participant has received their DNA analysis results – no further data will be collected after this point.

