## 8.5 Exploratory endpoints

The changes in expression of individual genes and key pathways induced by UA therapy

The changes in key stem cell and PgR target proteins induced by UA therapy

The changes in fibroglandular volume and other MRI/US elastography biomarkers

The changes in fibroglandular and fat tissue stiffness assessed by ultrasound elastography and acoustic radiation force imaging (ARFI)

The changes in breast impedance measured at baseline and 3 months.

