## 9 Specific protocols for endpoint analyses

### 9.1 Ki67 analysis

Samples will be transported to the Breast Biology Group laboratories in 10% formalin. After 24+/-6 hours in formalin (and with the exact time documented) samples will be embedded in paraffin in the pathology core facility at the CRUK Manchester Institute (CRUK-MI). Samples will be embedded in optimal cutting temperature cryo-sectioning media and snap frozen into a 2.5cm mould with liquid nitrogen cooled isopentane. Frozen sections (5um) will be cut at -20°C, air dried, washed in distilled H2O and stored at 4°C prior to use.

Paraffin sections will undergo antigen retrieval at 115 °C for 3 min (microwave processor) in Tris-EDTA buffer (pH 9.0) followed by staining with anti-MIB1 antibody at 1:200 dilution for 1 hour incubation at 37 °C. Following appropriate and uniform secondary antibody application and signal amplification the slides will be manually scored with the operator blinded to the sample time point (baseline or on treatment). For final analysis all samples will be stained and analysed at the same time to avoid between batch variability. However, local optimisation of the techniques using some of the samples may occur prior to this. The operator will count at least 1000 cells per sample where possible and score the percentage with nuclear Ki67 staining.

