### 9.4 Magnetic Resonance Imaging

Previous studies have demonstrated rapid reductions in background parenchymal enhancement (BPE) with SERM therapy in premenopausal women and greater reduction in BPE than FGV with transition from pre- to post-menopausal. We hypothesise that BPE will

also reduce in women sensitive to the effects of the antiprogesterin UA with three months of treatment. The primary imaging analysis will, therefore, be the change in BPE associated with UA therapy within individuals, scored according to the BI-RADS categories (minimal, mild, moderate and marked).

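### Elastography change includes the breast biopsied at baseline, the breast used for other imaging change is not stated, and the visual BPE score has no masking rule

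*Protocol*

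**What the plan says.** Elastography: Protocol section 8.3 states "Measurements of fibroglandular and fat tissue stiffness will be performed in each of the four quadrants of both breasts", aimed at the densest and least dense area of each quadrant. On timing it says "Ultrasound elastography will also be performed immediately prior to the vacuum biopsies", and on use "Changes in tissue stiffness between pre- and post-treatment scans will be explored and correlated with the MRI data". Section 8.5 lists elastography among the exploratory endpoints.

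Biopsy: section 4 places the baseline VAB in tissue "of the most dense region of one breast. Ideally 10 cores of breast tissue will be taken". The footnote to Appendix 5 puts MRI before VAB. The repeat MRI and the second tissue sample fall on Day 78-85 (section 7.1), and the second VAB is taken from the other breast.

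MRI: section 9.4 states "The primary imaging analysis will, therefore, be the change in BPE associated with UA therapy within individuals", scored in four BI-RADS categories, and expects BPE to fall in women sensitive to UA. Section 8.3 says BPE is measured visually and by regions of interest, and adds "The images will be viewed on a modality workstation and/or PACS workstation". Nothing is said about which breast is scored, the reading order, or whether the reader knows the time point.

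Ki67: section 9.1 requires that "the slides will be manually scored with the operator blinded to the sample time point (baseline or on treatment". No matching sentence covers the BPE read, colony typing (section 9.2) or picrosirius scoring (section 9.3).

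**The concern.** There are two gaps.

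- **Laterality.** The baseline scans show two uninjured breasts. The on-treatment scans show one uninjured breast and one that has had a large-volume biopsy in the kind of dense area that elastography targets. The protocol switches breasts for tissue but has no corresponding rule for imaging change.
- **Masking.** The BPE score is a four-category visual judgement with a stated expected direction. The protocol protects Ki67 from reader expectation but does not say that it protects BPE.

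In a single-arm trial no control group can separate a systematic pre-post artefact from a drug effect. Imaging also matters here: BPE change is a secondary endpoint (section 8.4.2), section 10 counts the search for imaging biomarkers among the study's primary aims, and section 3 intends those biomarkers for later randomised trials.

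**Working it through.** The plan has no imaging figure to reproduce. The sample of 30 rests on a cited study with 8 treated women, and no alpha, power, SD or imaging effect size is given. The steps below use protocol inputs where they exist and mark the rest as assumptions.

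**1. Tissue removed.** Section 8.2.1 plans 10 cores at about 100 mg each: 10 x 100 mg = about 1 g.

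**2. Interval from baseline VAB to on-treatment scan.** Inputs are the VAB window (from 11 days before expected menses to onset), the regularity criterion of 3 days either way (section 6.1), UA start within 1 week of onset, UA start counted as day 1, and the scan on Day 78-85.
- Shortest: VAB and UA start both on the day of onset, scan on day 78: 78 - 1 = 77 days, or 11 weeks.
- Longest: 11 + 3 + 7 + (85 - 1) = 105 days, or 15 weeks.

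**3. Share of elastography directly affected.** 4 quadrants x 2 breasts = 8 sites. One of 8 is affected over both breasts, one of 4 in the biopsied breast, and none in the other.

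**4. What a residual biopsy artefact could do (assumed).** Suppose there is no UA effect and the biopsied quadrant shifts by d, in units of the SD of the per-woman mean change. The mean over k quadrants then shifts by d/k. A paired t-test with n = 30 and two-sided 5% has noncentrality (d/k) x sqrt(30), which gives these false-positive rates:

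| d (SD) | both breasts, k = 8 | biopsied breast alone, k = 4 | other breast |
|---|---|---|---|
| 1 | 10% | 26% | 5% |
| 2 | 26% | 75% | 5% |
| 3 | 51% | 98% | 5% |
| 4 | 75% | about 100% | 5% |

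The same SD is used in both k columns. A four-quadrant mean would be noisier, so the k = 4 column is on the high side. The protocol names no test for elastography, so the t-test is also an assumption.

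**5. What reader drift in BPE could do (assumed).** Suppose there is no true change, a share b of reads moves one category each way by chance (10-20%), and a share q of women is read one category too low on treatment. Then P(up) = b(1 - q) and P(down) = b + (1 - 2b)q. An exact two-sided 5% sign test with n = 30 gives these false-positive rates:

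| q | false-positive rate |
|---|---|
| 0 | 1-2% |
| 10% | 6-8% |
| 20% | 17-28% |
| 30% | 36-57% |

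In the extreme case of k one-way moves and none back, p = 2 x 0.5^k: 0.063 for k = 5 and 0.031 for k = 6 (6 of 30 is 20%).

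**6. After the change.** With the breast not biopsied at baseline, the direct biopsy contribution is 0 and step 4 returns to 5%. With masked reads, q = 0 and step 5 returns to 1-2%.

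**The case against.** A reader might draw stronger conclusions, and the documents do not support them.

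- **All imaging change is pooled over both breasts.** Bilateral measurement is documented only for elastography, which is exploratory. For MRI and impedance the breast is unstated. Even for elastography, the sentence describes what is measured and gives no averaging rule.
- **Scans are read unmasked.** The protocol is silent. Reading on a clinical workstation does not show that dates are visible, and a SAP or imaging manual not shown here could set masking.
- **Biopsy injury does enter the UA effect.** Section 11.2 lists haematoma and scarring as risks, but nothing says that they persist at 11 to 15 weeks. Residual change could also run against the hoped-for reduction.
- **The p-value of 0.031 measures the problem.** It only illustrates six downward misreads with none upward. No document supports that rate.

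There is also partial protection in the plan. BPE is measured by regions of interest as well as by eye, section 9.5 aims for an objective method, and section 2.3 defines BPE as enhancement of normal glandular tissue, which a healing biopsy site is not.

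These points limit the claim without removing it. The regions of interest offer a cross-check, but section 9.4 makes the BI-RADS category the main imaging measure. Assessor masking is also a matter that section 9 already settles for Ki67, so setting it there for BPE is consistent with the plan's own practice.

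**Conclusion.** The point holds as a gap that is cheap to close. Elastography change includes the biopsied breast without any rule for it. The breast supplying change in BPE, FGV, ADC and impedance is unspecified. The visual BPE score lacks the time-point masking given to Ki67.

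Residual biopsy change and reader expectation may affect the apparent UA effect on imaging. The false-positive ranges above rest on assumed artefact size, drift, chance movement, tests and a 5% level, and are not estimates for this trial. The documents fix only the exposure: about 1 g from the densest region, one of 8 elastography quadrants, 11 to 15 weeks before the repeat scan.

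The primary endpoint is not affected: Ki67 scoring is masked, and the second VAB is in the breast not biopsied at baseline.

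**What to change.** - In sections 8.3, 9.4 and 10, name the breast not biopsied at baseline as the main contrast for change in BPE, FGV, ADC, elastography and impedance, and report the biopsied breast separately.
- In section 9.4, require stored MRI scans to be de-identified, stripped of dates and read for BPE in random order by the existing readers, masked to time point.
- The same masking sentence can be extended to colony typing and picrosirius scoring. It should not be extended to live elastography or impedance, where masking is not readily feasible.

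The cost is the anonymisation work and somewhat more measurement noise from using one breast. No extra participants, visits or readers are needed, and the sample size is unchanged. The change does not resolve the separate mismatch that baseline and on-treatment tissue come from different breasts, so correlations between imaging change and tissue change keep that limitation.
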